### Secondary Endpoints

#### Quality of Life

Descriptive statistics and diagrams will be used to characterize changes in Quality of Life metrics as measured by the EPIC-26. A linear mixed model with random intercept by an individual to account for the correlation present within individuals will be used to compare pretreatment vs. posttreatment quality of life measures at multiple timepoints with the goal of tracking minimally important differences in these parameters (57).

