We plan to evaluate the safety of SBRT with PSMA PET/MRI-guided focal boost in a prospective early phase trial, “PSMA MRI Guided prOstate SBRT(ARGOS).” As noted, while the advanced imaging techniques described show promise for the characterization of primary or recurrent prostate cancer, no study has prospectively and longitudinally evaluated them after primary radiotherapy to characterize expected changes in response to treatment and to non-invasively identify early treatment failure. All patients in ARGOS will enter the translational component of the study Comprehensive, Longitudinal Evaluation of Imaging Biomarkers Post Radiotherapy (CLIMBER). We will use advanced imaging analysis techniques to evaluate longitudinal changes in a comprehensive battery of anatomic and functional prostate imaging panels using ^18^F-PSMA 1007 and mpMRI acquired prior to and after SBRT. ^18^F-PSMA-1007 is chosen given its favorable pharmacokinetics profile with primarily gastrointestinal elimination, reducing tracer accumulation in the bladder and allowing better visualization of prostate and pelvic lymph nodes. The knowledge obtained from ARGOS/CLIMBER will improve the understanding of imaging changes post-prostate SBRT and will have increasing clinical importance with increasing use of these techniques. The ARGOS/CLIMBER protocol as outlined below is due to open in early 2022, with a plan for accrual of 50 men over 3 years and with follow-up of up to 5 years for clinical endpoints.

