**Figure 2 f2:**
[figure not shown]
Example of focal dose escalation.

**Table 3 T3:** Dose constraints.

Structures and dose constraints (acceptable deviations)			
**Rectum**	V20Gy ≤ 50% (optimal) V28Gy ≤ 15% (20%) V32Gy ≤ 10% (15%) V35Gy ≤ 2 cc (4 cc) V38Gy ≤ 1 cc Dmax ≤ 40.6 Gy	**Bladder**	V20Gy ≤ 50% (optimal) V28Gy ≤ 15% (20%) V32Gy ≤ 10% (15%) V38Gy ≤ 6 cc V39.5Gy ≤ 2 cc
**Rectum_PRV**	Dmax ≤ 45 Gy	**Bladder_PRV**	Dmax ≤ 46 Gy (optimal)
**Urethra_PRV**	Dmax ≤ 52 Gy D10% ≤ 47.2 Gy D50% ≤ 42 Gy (optimal)	**Penile Bulb**	V20Gy ≤ 40% (90%) V35Gy ≤ 4%
**Bowel_Small**	V25Gy ≤ 20 cc (40cc) V30Gy ≤ 2 cc Dmax ≤ 3 5Gy	**Bowel_Large**	V25Gy ≤ 20 cc (40 cc) Dmax ≤ 38 Gy
**Femur_R and Femur_L**	V28Gy ≤ 5%		

The primary endpoints of the trial will be 6-week and 6-month gastrointestinal (GI) and GU toxicity using the Common Terminology Criteria for Adverse Events version 5.0 (CTCAE v5.0). While other prospective trials have confirmed the safety of an mpMRI-defined intra-prostatic boost with external beam radiotherapy (4, 6), the proposed boost volume in ARGOS/CLIMBER will be based on mpMRI and PSMA PET-targeted PET (17), and thus there is a need to demonstrate the safety of such a multi-modality defined boost volume. Secondary endpoints include Quality of life measured by the Expanded Prostate Cancer Index Composite (EPIC-26) questionnaires and 5-year disease-free survival (DFS) as a composite of BF, patient death, or development of clinical metastases or institution of salvage ADT.

All grade 3 or higher toxicity will be reported to the principal investigator. An independent data and safety monitoring board (IDSMB) will perform a formal interim analysis for safety and toxicity when half of the patients have been accrued or after 1 year, whichever comes first. The study will be discontinued if the projected rate of grade 3 or higher urinary or bowel toxicity exceeds 30%. IDSMB will meet at least annually to review trial data.

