Unique to the ARGOS/CLIMBER protocol is the integration of longitudinal imaging with PSMA-directed PET and mpMRI pretreatment and posttreatment. Serial PSMA PET/MR images will be collected at baseline, 6 months, and 2 years to characterize the imaging response of prostate cancer to treatment and potentially identify imaging biomarkers (including pharmacokinetics, radiomics, and quantitative PET and mpMRI metrics) that predict for 5-year DFS (**Table 4**). Additionally, baseline collection of diagnostic tissue biopsy samples and serial collection of blood and urine over multiple time points (baseline, 6 months, 1 year, and 2 years post-SBRT) will be performed for correlative biologic biomarker analyses with imaging changes, DFS, and toxicity posttreatment. Analysis of prostate biopsy at baseline and 2 years will allow for correlation of histopathology with PSMA PET/MR images. We will investigate whether a negative posttreatment PSMA PET/MRI is correlated with a negative 2-year posttreatment biopsy and long-term disease control (36, 39). We also plan to examine novel clinical prognostic biomarkers (i.e., absolute percentage of Gleason Pattern 4 on biopsy and 4-year PSA response rate) and their correlation with imaging findings and 5-year DFS.

**Table 4 T4:** Schedule of events.

Event	Weeks (week 0 is start of RT)										Q6mo (30–60mo)
	−3	−2	0	1 EOT	3	8 (6 weeks post-RT)	6 months post-RT	12 months post-RT	18 months post-RT	24 months post-RT	
	V1	V2	V3	V4	V5	V6	V7	V8	V9	V10	V11–15
Start alpha antagonists, simethicone	x										
Fiducial marker insertion		x									
Simulation and planning		x									
Treatment (5 fractions q2d, 10–12 days)			x	x							
CTCAE v5.0	x		x	x	x	x	x	x	x	x	x
EPIC-26 questionnaires	x		x	x		x	x	x	x	x	x
PSA and testosterone	x					x	x	x	x	x	
PSMA PET/MRI		x					x			x	
Liquid biomarker collection		x				x	x	x		x	
Transperineal biopsy		x								x	

CTCAE v5.0, Common Terminology Criteria for Adverse Events version 5.0; PSA, prostate-specific antigen; PSMA, prostate-specific membrane antigen.

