### Primary Endpoint and Sample Size

This will be a single-phase pilot study of 50 patients with a primary endpoint of GI and GU toxicity as measured by CTCAE v5.0.

Unacceptable toxicity will be defined as acute (6 weeks) or intermediate (6 months) grade >3 GI or GU toxicity. The proposed treatment will be deemed too toxic if >30% of patients have unacceptable toxicity. This study tests the hypothesis that acute toxicity is <30% (alpha = 0.05, power = 81%, one-sided, H0: p = .30, HA: p <.30), with an assumed true proportion in this study of 15%. These calculations were done based on a Z test (normal approximation). We will test this assumption with the exact test approach if we do not meet our target accrual of 50 men or the proportion of Grade 3 toxicity is significantly less than 15% (conditions where normal approximation is not met).

Given that the proPSMA study demonstrated that 16% of men with high-risk prostate cancer had extra-prostatic disease beyond regional nodal metastases at initial staging and the fact our population will be a mix of high-intermediate and high-risk men, we will plan to enroll a total of 55 men (22). Those men with extra-prostatic spread beyond regional pelvic lymph nodes on their pretreatment PSMA PET imaging will be treated off protocol at the attending physician’s discretion.

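### The EPIC-26 model names only a patient random intercept, which with independent residuals gives every change from baseline the same standard error across 13 to 14 unevenly spaced visits over five years

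*Protocol article*

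**What the plan says.** The Study Design section of the Protocol article makes quality of life a secondary endpoint: "Secondary endpoints include Quality of life measured by the Expanded Prostate Cancer Index Composite (EPIC-26) questionnaires". The Quality of Life section plans descriptive statistics and then "A linear mixed model with random intercept by an individual to account for the correlation present within individuals". This model "will be used to compare pretreatment vs. posttreatment quality of life measures at multiple timepoints". Its stated aim is to follow minimally important changes in the scores. The section names no random slope, serial residual correlation, visit-specific variance or robust standard error. It does not state how time is coded.

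The row "EPIC-26 questionnaires" in Table 4 marks eight visits up to 24 months: V1, V3, V4 and V6 to V10. After that the schedule is six-monthly from 30 to 60 months. By month this is six more visits (14 in all); by the labels V11 to V15 it is five more (13 in all). The planned size is 50 men.

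**The concern.** A random intercept with independent residuals is compound symmetry. It has one variance, and the correlation between week −3 and week 0 equals that between week −3 and month 60. With a separate mean per visit and complete data, every change from baseline then has the same model-based standard error.

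This schedule makes that hard to accept. Visits are about a week apart around treatment and six months apart later, and five years separate the first from the last. Scores taken weeks apart would usually agree better than scores taken years apart, and pelvic radiotherapy may also widen the spread of scores for a time. The stated use is change from pretreatment at several visits, judged against minimally important differences, so visit-specific intervals are the product of this analysis. The 6-week and 6-month intervals fall at the times of the primary toxicity assessment. An interval that is too wide there can hide a decline; one that is too narrow at any visit can present noise as change.

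**Working it through.** **The plan's own figure.** The article states no figure for quality of life. Its only design calculation is for toxicity: "alpha = 0.05, power = 81%, one-sided, H0: p = .30, HA: p <.30", with an assumed rate of 0.15 and n = 50. It reproduces: Φ[(0.15·√50 − 1.645·√0.21)/√0.1275] = Φ(0.86) = 80.5%. It does not bear on this point.

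**Formulas.** Let V be the true covariance of the visits, with a mean per visit and complete data.
- Model variance of visit j minus baseline: 2·(mean variance − mean covariance)/n, the same for every j.
- True variance: (Vjj + V11 − 2·V1j)/n.
- Ratio = square root of model variance over true variance. Above 1 the interval is too wide, below 1 too narrow.
- Two-sided error at nominal 5%: 2·[1 − Φ(1.96 × ratio)].

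**One worked case (assumed).** Take unit variance and correlation 0.3 + 0.5·exp(−t/24), t in months, so 20% of the variance is visit-level noise. The average correlation over 14 visits is 0.52. Correlation with baseline is 0.75 at 6 weeks post-RT, 0.68 at 6 months and 0.34 at 60 months.
- Model SE, every visit: √(2 × 0.48/50) = 0.139 SD.
- True SE at 6 weeks: √(2 × 0.25/50) = 0.100 SD; ratio 1.39.
- True SE at 6 months: √(2 × 0.32/50) = 0.113 SD; ratio 1.23.
- True SE at 60 months: √(2 × 0.66/50) = 0.162 SD; ratio 0.86, error about 9%.

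**Range (assumed).** Correlation = (1 − noise) × [s + (1 − s)·d^years], with stable part s from 0.3 to 0.5, yearly decay factor d from 0.3 to 0.7, 14 visits, constant variance, and end of treatment placed at about 1.5 weeks:

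| Visit-level noise | Ratio, 6 weeks | Ratio, 6 months | Ratio, 60 months | Error, 60 months |
|---|---|---|---|---|
| 10% | 1.50–1.67 | 1.17–1.35 | 0.80–0.91 | 7.5–11.8% |
| 20% | 1.30–1.44 | 1.13–1.23 | 0.83–0.93 | 6.9–10.2% |
| 30% | 1.20–1.30 | 1.10–1.16 | 0.87–0.94 | 6.5–9.0% |

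With 13 visits instead of 14 (month 54 dropped), a middle case (s = 0.4, d = 0.5, 20% noise) moves by only about 0.01. Simulated fits of comparable decay patterns with 20% dropout gave 1.13–1.37 at 6 weeks and 0.75–0.90 at 60 months, with 8–13% error at 60 months. If the true correlation is constant and the variances equal, the ratio is 1.00 at every visit.

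**Unequal variance (assumed).** Take constant correlation 0.6 and SD 1.5 times larger at end of treatment and 6 weeks.
- Mean variance: (12 + 2 × 2.25)/14 = 1.179.
- Mean covariance: 0.6 × (15² − 16.5)/182 = 0.687.
- Model variance × n: 2 × (1.179 − 0.687) = 0.98.
- At 6 weeks, true variance × n = 2.25 + 1 − 2 × 0.6 × 1.5 = 1.45; ratio 0.82, error 10.7%.
- At later visits, true variance × n = 0.8; ratio 1.11.

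With the same SD pattern added to the decay grid above (s at 0.3 and 0.5), the ratios become 0.96–1.24 at 6 weeks, 1.20–1.49 at 6 months and 0.88–1.03 at 60 months. The 6-week and 60-month effects can therefore shrink or change sign; the 6-month interval stays too wide.

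**The case against.** The strongest objection is that the article never says the random intercept is the whole covariance model. Serial residuals or robust standard errors would fit the same sentence, and a condensed article commonly leaves such detail to the analysis plan, which is not shown. This stands in part: independent residuals are the plain reading, not a stated fact. But the sentence does give the random intercept as the means of handling within-person correlation, and read plainly that is a choice that suits this schedule badly.

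A reader might infer that early intervals are far too wide, with a 6-week type I error near zero. The documents do not support that. Ratios of 1.87–2.55 at 6 weeks arise only if EPIC-26 has no visit-level noise at all, which implies a correlation of 0.84 to 0.96 between baseline and 6 weeks, across a course of pelvic radiotherapy. Nor can a reader infer that early intervals must be too wide and late ones too narrow: the unequal-variance case reverses both.

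It is also fair that little depends on this. There is no quality-of-life hypothesis, alpha or power, descriptive statistics come first, and the setting is a single-arm pilot. That limits the weight of the point; it does not make the intervals right.

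**Conclusion.** The point holds as a should-fix on a secondary endpoint. The one correlation device named implies, with independent residuals, one standard error for every change from baseline over a five-year schedule.

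The size rests on assumptions, because the documents give no EPIC-26 standard deviation or correlation. With constant variance, decaying correlation and 10–30% visit-level noise, standard errors are about 20–65% too large at 6 weeks, 10–35% too large at 6 months and 5–20% too small at 60 months, where type I error is about 6.5–12%. Direction at 6 weeks and 60 months is not assured. Unless variance and correlation really are constant, the visit-specific intervals are unreliable one way or the other.

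With complete data and a mean per visit, the estimated changes themselves are unaffected. A reader might carry the problem over to the safety conclusion; the primary endpoint is CTCAE toxicity, tested as a proportion, and does not use this model.

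**What to change.** Keep the patient random intercept, treat visit as a factor, and report small-sample-corrected cluster-robust standard errors, clustered by man. These cover both decaying correlation and unequal variances; in simulations of decaying correlation, robust standard errors held type I error at 4–5.5%. Alternatively, add a serial residual correlation in actual time together with visit-specific variances; serial correlation with a common variance would leave the acute-phase problem in place. State the choice before the data are examined.

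The cost is about one line of code and no new data. Robust standard errors are slightly less stable with 50 men; the modelled alternative needs one or a few more covariance parameters.

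When Table 4 is next revised, reconcile the five labels V11 to V15 with the six visits implied by a six-monthly schedule from 30 to 60 months.

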#### Disease-Free Survival

Five-year DFS will be determined as a composite of biochemical control, patient death or development of clinical metastases, or institution of salvage ADT. DFS will be estimated with a Kaplan–Meier (KM) curve, with the 5-year estimate extracted from the KM curve.

#### Translational Imaging Endpoints

Changes in SUV metrics (SUVmax, SUVmean) within PSMA PET regions of interest (ROI) will be compared between the pre-RT PSMA PET and the 6-month post-RT PSMA PET. ROIs to be examined will include the dominant intra-prostatic lesions (DILs), the prostate as a whole, and, in the cases of men with PET-detected nodal disease, involved node ROIs. Descriptive statistics and diagrams (i.e., waterfall plots) will be used to characterize changes in SUV metrics. A linear mixed model with random intercept by an individual to account for the correlation present within individuals will be used to compare pretreatment vs. posttreatment SUV values at multiple timepoints. Overall response rates will be calculated in accordance with recent consensus guidelines (46).

Intra-prostatic mpMRI (T2W, DWI, and DCE-MRI) acquired pre-RT and 6 and 24 months post-RT will be reported by expert readers based on PI-RADS 2.1 and the complementary Prostate Imaging for Recurrence Reporting (PI-RR) system to identify intra-prostatic ROIs (44). Quantitative MRI metrics will be extracted, including ADC and pharmacokinetics parameters derived from dynamic PET and DCE-MRI. Radiomics approaches will be used to characterize the evolution of higher-level feature changes in PET and mpMRI over the course of treatment.

We will correlate changes in PET and mpMRI metrics at 6 and 24 months with 5-year DFS using linear regression models. We will also perform supervised machine learning to train support vector machines and random forest classifiers to predict response based on the pretreatment images. We will also perform a delta-radiomics analysis to predict response based on the radiomics trajectory computed from the first two time points. We will measure the performance of the classifiers using a cross-validation design, with metrics including the area under the receiver operating characteristic (ROC) curve and the error rate, false-positive rate, and false-negative rate computed at a point on the ROC curve that best balance the false-positive and false-negative rates. We will develop radiomics-based classifiers to predict 5-year DFS.

Baseline (pretreatment) and 24-month (posttreatment) tissue samples will be acquired for histopathologic correlations with PET/MR images. Specifically, baseline biopsy will provide histologic correlation for the PSMA- and mpMRI-identified dominant intra-prostatic lesions. Additionally, 24-month biopsies have been shown to correlate with long-term failure-free survival (36, 39), and rates of cancer clearance after stereotactic techniques have been shown to increase with increasing doses of radiation (58). Understanding histologic correlations and clearance of cancer from the boosted and non-boosted prostate areas will be of interest and will allow for correlation with PET/MR images to validate PET+MRI as non-invasive surrogates for identifying intra-prostatic cancer foci.

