**High intermediate risk**	
CTV_35Gy	Entire prostate including the GTVp_boost volumes
PTV_35Gy	CTV_35Gy + 3–4 mm
GTVp_boost	Intraprostatic GTV delineated as the union of mpMRI-defined PiRADS 4–5 intra-prostatic lesions with the PET-defined intra-prostatic lesions using threshold of 20% SUVmax (see text above). Where the seminal vesicle(s) are involved by PET or MRI, the involved portion will be included in the GTVp_boost volume(s)
PTVp_boost	GTVp_boost + 3–4 mm
CTV_ProxSV_25Gy	Proximal 1.0 cm of the seminal vesicles. The 1 cm of the seminal vesicles is measured superiorly from its origin at the prostate (not from the superior aspect of the prostate)
PTV_ProxSV_25Gy	CTV_ProxSV_25Gy + 4 mm

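### The SUV model has a random intercept per man only; if a man contributes more than one lesion or node, the standard error of the SUV change is miscalibrated, in either direction

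*Protocol article*

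**What the plan says.** All of this is in the protocol article.

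- **Regions measured** (Translational Imaging Endpoints): "ROIs to be examined will include the dominant intra-prostatic lesions (DILs), the prostate as a whole" and, further, "in the cases of men with PET-detected nodal disease, involved node ROIs". The whole prostate is one region per man. The number of lesions or nodes per man is not given.
- **Main contrast** (same section): SUVmax and SUVmean "will be compared between the pre-RT PSMA PET and the 6-month post-RT PSMA PET".
- **Model** (same section): "A linear mixed model with random intercept by an individual". Its stated purpose is to handle dependence among a man's own measurements, and no other random term is named. The article says that this model "will be used to compare pretreatment vs. posttreatment SUV values at multiple timepoints".
- **Scan times** (Study Design, paragraph before Table 4): "Serial PSMA PET/MR images will be collected at baseline, 6 months, and 2 years".
- **Several lesions foreseen** (Table 2): the boost volume is the union of the MRI-defined lesions "with the PET-defined intra-prostatic lesions using threshold of 20% SUVmax", so the plan allows for more than one lesion in a man.

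The Quality of Life section describes the same model for EPIC-26. There each man gives one questionnaire per visit, so no level lies between man and visit.

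**The concern.** Lesion-level SUV data have three levels: scan, within lesion or node, within man. An intercept per man covers only the top one. Two features are then left out.

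1. Two scans of the same lesion resemble each other more than scans of two different lesions in the same man. Without a lesion term, this stable difference goes into the residual. The pre/post comparison loses its pairing, and the standard error is too large.
2. Lesions in the same man may rise or fall together, because men differ in response. Without a man-level random change, the model treats these shared changes as independent, and the standard error is too small.

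Describing how imaging changes after SBRT is the stated purpose of the CLIMBER component, so the intervals around SUV change are among its main products. If miscalibrated, they could hide a real change or make an imprecise one look precise.

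**Working it through.** **Plan's own figures.** The article gives no power, SD, intraclass correlation or region count for SUV, so no stated SUV figure can be reproduced. Its one design calculation, for toxicity, does reproduce: Φ((0.15·√50 − 1.645·√0.21)/√0.1275) = Φ(0.859) = 80.5%, against a stated 81%. It does not involve SUV.

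**Inputs.** From the article: n = 50 men and the baseline versus 6-month contrast (two scans). Assumed, and varied: m regions of one type per man; s_u, the SD between regions within a man; s_c, the SD between men of the change; and s_e = 0.5, the residual SD. The between-man SD of the level drops out of the contrast.

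**Formulas (balanced data).**
- True SE of the mean change: √(s_c²/n + 2s_e²/(nm)).
- SE reported with a man intercept only: √(2·MS/(nm)), where MS = [(n−1)(m·s_c²/2 + s_e²) + n(m−1)(2s_u² + s_e²) + n(m−1)s_e²] / [n(2m−1) − 1].
- Approximate coverage of a nominal 95% interval: 2Φ(1.96 × ratio) − 1.

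**Too wide: m = 2, s_u = 1, s_c = 0.** MS = (12.25 + 112.5 + 12.5)/149 = 0.921. Reported SE = √(2 × 0.921/100) = 0.136. True SE = √(0.5/100) = 0.071. Ratio 1.92.

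**Too narrow: m = 2, s_u = 0.3, s_c = 1.** MS = (61.25 + 21.5 + 12.5)/149 = 0.639. Reported SE = √(2 × 0.639/100) = 0.113. True SE = √(0.02 + 0.005) = 0.158. Ratio 0.72.

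| Regions per man | s_u | s_c | Reported / true SE | Coverage |
|---|---|---|---|---|
| 1 | – | 0, 0.5 or 1 | 1.00 | 95% |
| 2 | 0.5 | 0 | 1.29 | 98.9% |
| 2 | 0.7 | 0 | 1.52 | 99.7% |
| 2 | 1 | 0 | 1.92 | ~100% |
| 3 | 1 | 0 | 2.05 | ~100% |
| 2 | 1 | 0.5 | 1.42 | 99.5% |
| 2 | 0.5 | 0.5 | 1.00 | 95% |
| 2 | 1 | 1 | 1.00 | 95% |
| 3 | 1 | 1 | 0.88 | 91.5% |
| 2 | 0.3 | 1 | 0.72 | 84% |
| 3 | 0.3 | 1 | 0.59 | 76% |

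Eight of these settings were also simulated, with 4,000 trials each. The ratios agreed to within about 0.04, and man-only coverage in the multi-region cases ran from 75% to 100%. An SE built from each man's mean change gave 94% to 96% in every case.

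**Would a region-within-man intercept alone be enough?** Its residual mean square is [(n−1)(m·s_c²/2 + s_e²) + n(m−1)s_e²]/(nm − 1). With m = 2 and s_c = 0.5 this is (24.5 + 12.5)/99 = 0.374. The reported SE is 0.086 against a true 0.100: ratio 0.86, coverage 91%. With s_c = 1 the ratio is 0.77 and coverage 87%. That term corrects the estimate only when all men change equally (s_c = 0).

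**The case against.** **The data structure is not documented.** The article does not say that each lesion or node is its own row, that region types are pooled, or how many lesions a man has. The plural for lesions could describe the cohort, and nodes concern only some men. With one value per man per scan (whole prostate, one index lesion, or a per-man summary), the stated intercept gives the right standard error for the two-scan contrast. This stands, and it makes the point conditional.

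**A condensed article leaves the unit of analysis to the full protocol or the SAP.** This stands in part: silence on the unit of analysis is not a fault here. But the article does state the random term and what it is for. Table 2 allows several lesions per man, and with lesion-level rows the stated term does not do that job.

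**A reader might infer that the error bars are simply wrong, or always too wide, so that real changes will be missed.** The documents do not support this. Inflation in every case requires that all men change by the same amount. The article gives no basis for that, and its search for imaging biomarkers of response presumes that men differ. Under equal change, a lesion SD of 0.7 and a true change of 0.2 would cut power from about 81% to about 44% (normal approximation). That figure belongs to that one case. Elsewhere in the table the error reverses or cancels.

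**The analysis is exploratory.** This is correct. The toxicity endpoint, the safety stopping rule and the sample size do not use it, and the planned descriptive summaries and waterfall plots are unaffected.

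**Conclusion.** The point holds conditionally. If more than one lesion or node per man enters the stated model, the standard error of the SUV change is generally miscalibrated. Over the assumed settings it is 0.59 to 2.05 times the true value, with nominal 95% coverage from about 76% to nearly 100%. The direction depends on two variances that the model does not separate and the article does not give. The model is calibrated only where their effects happen to cancel. With one value per man per scan there is no problem for the baseline to 6-month contrast.

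These sizes rest on assumed SDs, balanced data, 50 men and two or three regions per man. They show the possible range and do not predict this trial's result. The consequence is confined to the translational SUV analysis.

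**What to change.** - State the unit of analysis, and fit dominant lesions, whole prostate and nodal regions in separate models.
- Where a man contributes several lesions or nodes, either add a region-within-man random intercept **together with** a man-level random change, or use standard errors clustered by man. A region intercept alone should not be adopted, because it gives intervals that are too narrow when men differ in their change.
- A simpler alternative is to reduce the data to one summary value per man per scan and keep the stated model for the two-scan contrast.

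The cost is a few words in the plan and slightly more complex modelling. With few node-positive men the fuller model may not be estimable for nodes, and the per-man summary is then the practical choice. No new data are needed, and the primary endpoint and sample size do not change.

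### Linear regression is the stated model for relating imaging change to 5-year DFS, a censored outcome, and part of that outcome will already have occurred by the 24-month scan

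*Protocol article*

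**What the plan says.** Under Translational Imaging Endpoints, the model for imaging change and outcome is named: "We will correlate changes in PET and mpMRI metrics at 6 and 24 months with 5-year DFS using linear regression models". The same paragraph plans radiomics classifiers for 5-year DFS.

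The Disease-Free Survival section defines the outcome: "Five-year DFS will be determined as a composite of biochemical control, patient death or development of clinical metastases, or institution of salvage ADT". It then says how DFS is summarised: "DFS will be estimated with a Kaplan–Meier (KM) curve, with the 5-year estimate extracted from the KM curve".

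On follow-up, the end of Introduction and Background describes the trial "with a plan for accrual of 50 men over 3 years and with follow-up of up to 5 years for clinical endpoints". On timing, Study Design says "Serial PSMA PET/MR images will be collected at baseline, 6 months, and 2 years", and the biomarkers sought are those "that predict for 5-year DFS". Study Design also lists clinical markers to be related to imaging and 5-year DFS, namely "absolute percentage of Gleason Pattern 4 on biopsy and 4-year PSA response rate".

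The article names no survival regression model for the imaging analysis, and no rule for men whose DFS event comes before a scan.

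**The concern.** Two separate problems follow from the stated method.

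- **Censoring.** Kaplan–Meier is used because some men will not be observed to an event or to 5 years. Linear regression needs a complete numerical response from every man. Whether that response is observed time or 0/1 status, a man censored before 5 years does not have one, and any value given to him is a choice that moves the slope.
- **Order in time.** The aim is prediction, but DFS spans the whole 5 years while the last scan is at 24 months. A man who has failed biochemically or started salvage ADT by then has already had his DFS event. Keeping him in the model lets the scan reflect the failure it is supposed to predict.

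At stake is the reading of the imaging biomarkers. Estimated associations could be diluted or exaggerated by how censored men are handled, and a 24-month marker could look predictive because it registers failures already known.

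**Working it through.** **The plan's own figure.** The article gives no power or event count for this analysis. Its one power statement, "alpha = 0.05, power = 81%, one-sided, H0: p = .30, HA: p <.30", concerns toxicity. With n = 50 and an assumed true rate of 15% it reproduces: Φ[((0.30 − 0.15)√50 − 1.645√(0.30 × 0.70)) / √(0.15 × 0.85)] = Φ(0.859) = 80.5%. It does not bear on this point.

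**Inputs.** From the article: n = 50, scans at 6 and 24 months, 3-year accrual. The article gives no expected DFS for this trial; the only 5-year rates in it are the 92% and 85% biochemical DFS of the FLAME arms in Table 1. Assumed: 5-year DFS of 92%, 85%, 80% and 70%, exponential times, a hazard ratio of 2 per SD of imaging change, and loss of 0, 4% or 5% a year.

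**1. Men with unknown 5-year status.** At 4% a year, 1 − 0.96⁵ = 0.185, or about 9 of 50 before allowing for events; simulation gives 8 to 9. At 2% and 5% a year (DFS 80%) it is about 4 and 10.

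**2. Observed time as response.** Power at two-sided 5%, n = 50; ranges are across independent simulation runs:

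| 5-year DFS | Linear on time, 4% loss | Cox, 4% loss | Linear on time, no loss | Cox, no loss |
|---|---|---|---|---|
| 80% | 24–27% | 49–50% | 46% | 54% |
| 85% | 16–19% | 34–41% | 37% | 43% |
| 92% | 11–12% | 18–22% | 22% | 23% |

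Most of the shortfall comes from the assumed loss. The slope also shrinks (DFS 80%, 5% loss a year): −0.275 against a true −0.323 when every man has 5 years of potential follow-up.

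**3. 0/1 status as response.** Dropping men of unknown status, power at 4% loss is 48.5–50.5% at DFS 80%, about 42% at 85% and 22% at 92%, much like Cox. The slope for event-free status depends on the handling (DFS 80%, 5% loss a year):

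| Follow-up | Censored men | True slope | Censored counted event-free | Censored dropped |
|---|---|---|---|---|
| 5 years possible for all | about 10 | −0.115 | −0.103 | −0.125 |
| Data cut 6.5 years after first accrual | about 26 | −0.115 | −0.099 | −0.160 |

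The two choices err in opposite directions, and the article picks neither. With 5 full years and no loss, this bias disappears.

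**4. Events before the scan.** With 5-year DFS = S, expected events are 50(1 − S) by 5 years, 50(1 − S^0.4) by 24 months and 50(1 − S^0.1) by 6 months:

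| S | By 5 years | Before 24 months | Share | Left after 24 months | Before 6 months |
|---|---|---|---|---|---|
| 92% | 4.0 | 1.6 | 41% | 2.4 | 0.4 |
| 85% | 7.5 | 3.1 | 42% | 4.4 | 0.8 |
| 80% | 10.0 | 4.3 | 43% | 5.7 | 1.1 |
| 70% | 15.0 | 6.6 | 44% | 8.4 | 1.8 |

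Complete follow-up does not remove this problem.

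**The case against.** The strongest reply is that 5-year DFS reads naturally as status at 5 years, the more so since the same paragraph plans classifiers for it. On that reading power matches Cox, and with full follow-up there is no censoring bias. This stands as far as power goes, so the power loss is tied to the observed-time reading and to an assumed loss rate. It does not rescue the method: follow-up is only up to 5 years, men of unknown status still need a rule, and the 24-month ordering problem remains.

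A second reply is that a condensed article may leave a landmark to the full protocol. That is fair for the landmark taken alone. The linear model, however, is stated, and it conflicts with the article's own treatment of DFS.

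Several stronger readings are tempting but unsupported:

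- A reader might infer that the tests are invalid. Under no effect, with non-informative loss, linear regression rejected in 4.3–5.9% of runs at a nominal 5%. The faults are biased slopes, possible loss of power and time order, not inflated false positives.
- A reader might infer that men who reach the 24-month scan are event-free by selection. Nothing in the article stops imaging after failure, and Table 4 schedules that scan without such a condition.
- A reader might infer that relating 4-year PSA response to 5-year DFS is circular. The article neither defines that marker nor names a model for it, and the linear-regression sentence covers imaging metrics only. The overlap with biochemical failure is a caution, not a demonstrated error.

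**Conclusion.** The concern holds at moderate severity. The stated model does not suit the outcome as the article itself defines and estimates it. The damage depends on the response used: smaller slopes and lower power for observed time, or a slope that depends on an unstated handling of lost men for 0/1 status. At assumed DFS of 80–92%, about 1.6 to 4.3 of 4 to 10 expected events would precede the 24-month scan; the problem is minor at 6 months.

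These sizes rest on assumed DFS, hazard ratio, loss and exponential times. The direction of the bias in the observed-time slope, and the need for a rule for lost men, do not depend on the particular values once some men are censored before 5 years.

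A reader might take this as a flaw that undermines the trial. It does not: this is a translational analysis in a 50-man pilot with a toxicity primary endpoint, and neither that endpoint nor its sample size depends on it.

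**What to change.** - Replace linear regression on 5-year DFS with Cox models, Firth-penalised and limited to very few predictors, landmarked at the scan date. Include men event-free and in follow-up at 6 (or 24) months and count DFS from that scan.
- For the 5-year DFS classifiers, use a censoring-aware target, such as inverse-probability-of-censoring weights or a survival forest.
- If 4-year PSA response is related to 5-year DFS, restrict that analysis to men event-free at 48 months, or report it descriptively.

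The change is to wording only and uses the same data; it should be made before outcomes are seen. The cost falls on the 24-month analysis. About 2 to 4 men with earlier events leave it at DFS of 92–80%, and about 6 at lower DFS: 50(1 − 0.74^0.4) = 5.7 at 74%, and 6.6 at 70%. Roughly 2 to 8 events remain. Under the 4%-loss assumptions, landmarked Cox power at 24 months is only about 27%, 21% and 10% at DFS of 80%, 85% and 92%. The plan should therefore call these results hypothesis-generating.
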